### Prohibited Concomitant Medications

There are no prohibited concomitant medications.

### Management of SSI After Occurrence

The treatment approach for perineal wound SSI is not predefined (left to institutional policy). No restrictions are placed on additional treatment after completion or discontinuation of the study intervention.

### Surgical Considerations

No restrictions are placed on the extent of lymph node dissection, preservation of autonomic nerves, or the approach to sigmoid colostomy. The surgical approach will be laparoscopic or robotic-assisted, and open surgery is excluded.

## Discontinuation Criteria

A participant’s continuation in the study may be discontinued under the following conditions:

1. The participant is enrolled but does not receive pNPWT postoperatively.
2. The participant requests withdrawal of treatment or consent is revoked.
3. It is determined after treatment initiation that the participant does not meet the eligibility criteria.
4. The principal investigator or sub-investigators deem that continuing the study poses safety concerns.

If a participant withdraws consent, the investigator will confirm whether the data collected up to that point may still be used in the study. If the participant refuses all data use, the study office will be informed accordingly.

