| Key  Inclusion & Exclusion Criteria | Inclusion Criteria | 1) Patients undergoing abdominoperineal resection (APR) for rectal malignancies.  2) Patients meeting the insurance coverage criteria for the PREVENA incision management system, specifically:  (a) Patients who underwent neoadjuvant therapy (chemotherapy, chemoradiotherapy, or both).  (b) Obese patients with a BMI ≥ 30.  (c) Diabetic patients with HbA1c (NGSP) ≥ 7.0%.  (d) Patients receiving steroid therapy.  (e) Patients undergoing chronic maintenance dialysis.  (f) Patients with malnutrition (meeting one of the following criteria):  3) Patients aged 18 years or older, regardless of gender, with an ECOG Performance Status (PS) of 0 or 1.  4) Obtain written consent to participate in the study |
|  | Exclusion Criteria | 1) Emergency surgery cases.  2) Cases with obviously contaminated/infected wounds where primary closure is not advisable.  3) Myocutaneous flap reconstruction is scheduled to be performed.  4) Patients with allergies or hypersensitivity to silver or acrylic adhesives.  5) Other cases deemed inappropriate for study participation by the principal or sub-investigators |
|  | Minimum Age | 18 years |
|  | Maximum Age | None |
|  | Gender | Both male and female participants are eligible |
| Discontinuation Criteria | | 1) The participant was registered but did not receive prophylactic negative pressure wound therapy (pNPWT).  2) The participant requests discontinuation of treatment or withdrawal of consent.  3) The participant is found to be ineligible after the start of treatment.  4) The principal or sub-investigator determines that continuation of the study is difficult for safety or other reasons. |
| Target Disease | | Rectal malignancies |
| Intervention Details | | Following primary suture closure of the perineal wound after APR, prophylactic negative pressure wound therapy (pNPWT) using the Prevena Plus Customizable Kit will be applied for one week. |
| Primary Outcome(s) | | Incidence rate of surgical site infection (SSI) in the perineal wound within 30 days postoperatively. |
| Secondary Outcome(s) | | Incidence of postoperative complications other than perineal SSI.  Postoperative hospital stay duration.  Completion rate of pNPWT. |

Shema

[figure not shown]

Table of Contents

[1. Background and Significance 9](#_Toc191825328)

[1.1. Target Disease and Previous Studies Related to This Research 9](#_Toc191825329)

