## Target Sample Size and Rationale for Determination

The target sample size for this study is 50 patients.

< Rationale for Sample Size Calculation >

Existing reports indicate that the incidence of perineal wound SSI in patients receiving pNPWT ranges from 9.1% to 14.8%, whereas the incidence in patients not receiving pNPWT ranges from 32.6% to 41.7% ^(18,20)^. This study assumes that the incidence of perineal wound SSI within 30 days postoperatively will be 12%, with a threshold of 40% based on prior reports. Given a two-sided significance level of 5% and a power of 80%, the required sample size is 45 patients. To account for potential dropouts, the planned enrollment target is set at 50 patients.

< Estimated Patient Accrual >

The participating institutions collectively treat approximately 80 patients per year who meet the eligibility criteria. Assuming an eligibility rate of 70% and a consent rate of 70%, it is expected that 50 patients can be enrolled within 15 months.

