# Study Completion, Early Termination, Suspension, and Resumption

## Study Completion

This study will be considered complete when all enrolled cases have completed the 30-day postoperative follow-up period, all data collection and analysis have been finalized, and the final study report has been compiled.

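### Section 6.3 lets a patient who only asks to stop pNPWT be taken out of the study, and no text secures the day-30 SSI assessment afterwards

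*Protocol*

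**What the plan says.** Section 6.3 opens with "A participant’s continuation in the study may be discontinued under the following conditions". Its second ground is "The participant requests withdrawal of treatment or consent is revoked". Its fourth is "The principal investigator or sub-investigators deem that continuing the study poses safety concerns". The Overview has a matching entry, "The participant requests discontinuation of treatment or withdrawal of consent", and its own fourth ground is wider, since it admits reasons other than safety.

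The only data rule in 6.3 concerns withdrawn consent: "the investigator will confirm whether the data collected up to that point may still be used in the study". It looks back at data already held and does not address later follow-up.

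The primary outcome (9.1) is perineal wound SSI up to 30 days after surgery. The device is worn for 7 days (6.2.1). Section 17.1 states: "This study will be considered complete when all enrolled cases have completed the 30-day postoperative follow-up period".

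**The concern.** Stopping a device and leaving a study are different events, and 6.3 does not separate them. A patient who asks on day 3 to have the dressing removed meets a listed ground for ending study participation. About 27 days (30 − 3) of the outcome window would then have no stated follow-up.

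Such requests are foreseeable. Section 11.2 names discomfort, skin damage and delayed detection of infection as burdens or risks of the device. If some exits are prompted by a wound that is not doing well, the patients lost have a higher SSI risk than those who stay. There is no control arm in which a similar loss could offset this. The proportion with its 95% confidence interval (12.2.1) is the whole primary result, and section 1.3 intends the data as the basis for a larger trial.

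A statistical analysis plan can say how missing outcomes are handled, but it cannot recover outcomes that sites did not collect. Routine care is only a partial substitute, because 9.3 requires a checklist and independent assessment by two clinicians, and that process may not be run for a patient already discontinued.

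**Working it through.** **Step 1: set the sections side by side.**

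| Section | What it implies for a patient who stops early |
| --- | --- |
| 6.3, ground 2 | A request to stop treatment can end study participation |
| 6.3, ground 4 | A safety judgement about continuing the study can end it |
| Overview | Similar grounds, without the lead-in about continuation in the study |
| 6.2.1 | After removal for an adverse event the device is not reapplied; nothing about leaving the study |
| 8.2.2 | The day of premature removal is recorded, next to the SSI outcome |
| 9.2 | The 7-day completion rate needs early stoppers in its denominator |
| 10.1 | Adverse events are reported to at least day 30 |
| 12.1.1 | Partial application is enough for the safety set |
| 12.1.2 | The efficacy set requires application and no major violation, not 7 days of wear |
| 17.1 | All enrolled cases are expected to finish 30 days of follow-up |

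The last seven rows imply that early stoppers stay in. None of them tells a site what to do when a patient asks to stop, and membership of an analysis set does not supply an outcome that was never collected.

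**Step 2: inputs for an illustration.** The protocol gives no figure for lost outcomes. The nearest is the dropout allowance in 12.3: 50 − 45 = 5 patients, 10% of 50. Assume, for illustration only, that all 5 are treated patients without a day-30 outcome. At the assumed 12%, 45 patients would have 45 × 0.12 = 5.4 SSIs, so take 6 as observed.

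**Step 3: range over all 50.** The intervals are exact (Clopper-Pearson), also an assumption because 12.2.1 names no method. With x events in n, the lower limit is the 0.025 quantile of Beta(x, n − x + 1) and the upper limit is the 0.975 quantile of Beta(x + 1, n − x).

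| Case | Rate | 95% CI |
| --- | --- | --- |
| Observed | 6/45 = 13.3% | 5.1 to 26.8 |
| None of the 5 had SSI | 6/50 = 12.0% | 4.5 to 24.3 |
| 2 of the 5 had SSI | 8/50 = 16.0% | 7.2 to 29.1 |
| All 5 had SSI | 11/50 = 22.0% | 11.5 to 36.0 |

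**Step 4: direction.** Let m of 50 be lost with SSI risk q, and let the others have risk r = 12%. The complete-case rate minus the all-treated rate is (m/50) × (r − q).

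- m = 5: 0 points at q = 12%; −1.2 at 24%; −2.8 at 40%; −4.8 at 60%.
- m = 2: 0 to −1.9 points over the same values of q.
- m = 10: 0 to −9.6 points.

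For q below 12% the sign reverses. If the lost patients were instead kept in the denominator as free of SSI, m = 5 would give 45 × 0.12 / 50 = 10.8%, which is too low for any q above zero.

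**Step 5: the 40% threshold.** With n = 50 the exact upper limit stays below 40% for up to 12 SSIs. The worst case in step 3 has 11. With 5 lost, the threshold comparison is safe whatever their outcomes, as long as no more than 12 − 5 = 7 SSIs are observed.

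**The case against.** Much of the protocol points the other way, as the table shows. Section 6.2.4 even speaks of discontinuing the study intervention as an event of its own. On this view the defect is one loose line, permissive at that (it says that continuation may be ended), and sites would follow these patients anyway. An SSI diagnosed at or before exit is already counted, and data collected earlier are kept unless the participant refuses (5.3, 6.3). The handling of missing outcomes may be set out in an analysis plan not shown here.

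Most of this stands, and it rules out four stronger readings that a reader might infer:

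- **That any removal of the device ends participation.** Removal as such is not a listed ground. A participant's request is, and so is an investigator's judgement about continuing the study.
- **That the rate is biased downward.** The direction depends on who leaves. Discomfort has no stated link with infection, and exits for discomfort alone may cause no bias.
- **That 12.3 plans for these losses.** It says only "To account for potential dropouts, the planned enrollment target is set at 50 patients". Dropouts may equally be patients who never received pNPWT or proved ineligible, both of which are separate grounds in 6.3.
- **That the result against 40% is in danger.** The worst case above has an upper limit of 36.0%. Its rate of 22.0% is about 1.65 times the observed 13.3%, and it needs every lost patient to have had an SSI.

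The objection does not remove the gap itself. The one section that deals with discontinuation allows exit on a request to stop treatment, and no section says that SSI assessment then continues to day 30.

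**Conclusion.** The point holds as a conflict between sections with a real risk of lost primary outcomes. It does not hold as a rule that excludes every patient whose device comes off. Under 6.3, treated patients who stop early can lose the day-30 SSI assessment that 17.1 and the analysis sets presuppose.

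The SSI rate may then be biased, probably downward where exits follow safety or wound concerns. With 5 of 50 lost and 6/45 observed, the all-treated rate is known only to lie between 12.0% and 22.0%. Under the milder assumptions in step 4 with 5 lost, the complete-case rate is 0 to 4.8 points too low. The number lost, their SSI risk and the observed count are all assumptions. What is at stake is the estimate and its use in planning a later trial; in this illustration the comparison with the 40% threshold is unchanged.

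**What to change.** In 6.3 and in the Overview, replace the single list with two.

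- **(a) Discontinuation of pNPWT**, whether at the participant's request, for an adverse event or by investigator decision. The patient stays in the study, and perineal SSI (by the 9.3 procedure), other complications and adverse events are collected to day 30 as for every other patient.
- **(b) Withdrawal from the study.** Data collection ends only when the participant revokes consent to further data collection. The existing rule on data already held then applies.

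Both places would then agree with 12.1.1, 12.1.2 and 17.1. The change concerns data collection only and does not touch when or why the device is stopped. No change in sample size is needed. The cost is a wording amendment through the usual approval, plus continued follow-up of a few patients who are already seen in routine postoperative care. It should be made before outcomes are lost, because they may not be recoverable later.

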## Post-Study Treatment

No restrictions are placed on treatments administered after study completion or early termination (left to institutional policy).

# Investigational Device

## Overview of the Investigational Device

The pNPWT device used in this study is the:

・3M™ Prevena Plus Customizable Kit

## Device Classification

Class III (under Japan’s medical device classification system).

## Distribution, Storage, Management, and Return of the Device

Since this device is an approved medical device, it is routinely available in the operating rooms of participating institutions. During the study period, it will be managed and stored in the same manner as in regular clinical practice.

The principal investigator will confirm that each participating institution has appropriate protocols for the storage, management, and use of the device.

## Dentification and Prevention of Misuse

Since this device is also used in standard clinical practice, no special labeling or additional identification measures will be implemented.

# Study Procedures

## Patient Enrollment Procedures

After obtaining informed consent, the principal investigator or sub-investigators will assess eligibility based on the criteria outlined in 8.2. Observation, Examination, and Reporting Items. If eligibility is confirmed, patient enrollment will be recorded in an electronic data capture system (REDCap).

Contact Information for Enrollment Inquiries:

・Kyoto University Hospital, Department of Surgery

・Address: [name]

・[contact] (Weekdays, 9 AM – 4 PM)

・Email: [contact]

## Observation, Examination, and Reporting Items

### Baseline (Preoperative) Patient Information

Eligibility will be confirmed based on the following baseline information.

Clinical tests performed within 14 days before surgery will be considered valid.

1. Patient background information

Date of birth, date of consent, age at consent, sex.

1. Physical examination

Height, weight, BMI, ECOG-PS.

1. Primary disease information

TNM classification (clinical stage), tumor location, histological type (including carcinoma, GIST, and NET). (Following Japanese Classification of Colorectal, Appendiceal, and Anal Carcinoma, 9th Edition ^(22)^.)

1. Laboratory tests

WBC, Neu, Hb, PLT, T-Bil, AST, ALT, LDH, ALB, CRP, CRE, eGFR, CCr, Na, K, Cl, HbA1c (NGSP)

1. Smoking status (Brinkman index)
2. Presence of chronic dialysis
3. Use of steroids
4. Comorbid inflammatory bowel disease (IBD)
5. Diabetes mellitus
6. Preoperative treatment history

NAC、NACRT、TNT

### Surgical and Postoperative Information

Clinical tests will be conducted on postoperative day 1 (±1 day allowed), day 3 (±1 day allowed), and day 7 (±2 days allowed).

Surgical information, hospitalization details, surgical outcomes, and pathology results will be recorded as needed.

1. Surgical Information

Date of surgery, duration of surgery, type of disinfectant used, estimated blood loss, presence of blood transfusion, type of antibiotics used.

Abdominal approach: Laparoscopic, robotic-assisted.

Perineal approach: Open, endoscopic.

Skin closure method (interrupted sutures, subcutaneous buried sutures) and type of suture used.

Amount of saline used for wound irrigation.

Lateral lymph node dissection (LLND): Presence or absence (if present, specify left or right).

1. Laboratory Tests

WBC, CRP, other abnormal values (CTCAE Grade ≥2).

1. Hospitalization and Discharge Information

Date of admission, date of discharge or transfer.

1. Surgical Outcomes

Postoperative complications (perineal wound SSI and other complications).

Whether pNPWT was maintained for the full 7-day period.

If pNPWT was removed prematurely, specify on which postoperative day.

1. Pathology Results

ypTNM classification, surgical margin status, assessment of response to chemotherapy.

(Following Japanese Classification of Colorectal, Appendiceal, and Anal Carcinoma, 9th Edition ^(22^).

## Study Schedule

The study schedule is outlined in the table below. Routine postoperative clinical and imaging examinations may be performed as needed, regardless of this schedule.

[figure not shown]

# Evaluation Criteria

## Primary Outcome

1. Incidence of perineal wound SSI

The proportion of patients who develop perineal wound SSI from the time of enrollment until 30 days postoperatively. SSI includes superficial incisional SSI, deep incisional SSI, and organ/space SSI. If a single patient develops multiple SSIs (e.g., both superficial incisional SSI and organ/space SSI), they will be counted as one case.

Diagnosis of SSI will follow the definitions published by the Centers for Disease Control and Prevention (CDC) in the National Healthcare Safety Network (NHSN) criteria ^(21)^.

## Secondary Outcomes

1. Incidence of postoperative complications other than perineal wound SSI

The proportion of patients who experience complications classified as Grade III or higher on the Clavien-Dindo classification scale.

1. Postoperative length of hospital stay

The duration from the date of surgery to discharge or transfer.

1. Completion rate of pNPWT

The proportion of patients in the pNPWT group who successfully maintained pNPWT application for 7 days postoperatively.

## Criteria for Diagnosing SSI

SSI's diagnostic criteria follow the CDC's published definition ^(21^).

SSI will be diagnosed according to the definitions published by the CDC ^(21)^. A checklist will be used to confirm the diagnosis based on signs and symptoms. Two clinicians (at least one of whom must be a board-certified surgeon) will independently evaluate the case. If their assessments differ, a third board-certified surgeon will be consulted to make the final determination.

The wound dehiscence with signs of infection will be classified as SSI. The wound dehiscence without signs of infection will be classified as a postoperative complication other than SSI.

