# Study Design

## Overview of Study Design

This study is a multicenter, single-arm, open-label, non-controlled interventional trial.

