### Superficial incisional SSI

A case will be classified as superficial incisional SSI if all of the following conditions are met:

1. The infection occurs within 30 days postoperatively.
2. The infection is limited to the skin and subcutaneous tissue.
3. At least one of the following criteria is met:
4. Purulent discharge from the superficial incision.
5. Organisms isolated from aseptically obtained fluid or tissue from the superficial incision.
6. The superficial incision is deliberately opened by the surgeon, with or without positive culture, and at least one of the following symptoms is present: pain, tenderness, localized swelling, erythema, or heat. A negative culture result does not meet this criterion.
7. The attending physician or surgeon diagnoses the condition as superficial incisional SSI.

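### Both SSI assessors may come from the operating team in this open-label, single-arm trial; one of the two should be a non-operator

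*Protocol*

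**What the plan says.** Section 9.1 defines the primary outcome as "The proportion of patients who develop perineal wound SSI from the time of enrollment until 30 days postoperatively". Section 9.3 sets out how a case is judged:

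- Diagnosis follows the CDC definitions, with a checklist of clinical findings as support.
- On the assessors it says: "Two clinicians (at least one of whom must be a board-certified surgeon) will independently evaluate the case".
- Disagreement between the two goes to another board-certified surgeon, whose decision is final.
- A dehisced wound counts as SSI when it looks infected. Otherwise it falls outside the primary endpoint: "The wound dehiscence without signs of infection will be classified as a postoperative complication other than SSI".

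Sections 9.3.1 to 9.3.3 list the qualifying criteria for each type of SSI. The attending clinician's own diagnosis is one of them; for the superficial type it reads "The attending physician or surgeon diagnoses the condition as superficial incisional SSI".

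Section 6.1 describes the trial as a "multicenter, single-arm, open-label, non-controlled interventional trial". Section 12.3 assumes a 12% rate against a 40% threshold taken from earlier reports and sets enrolment at 50. Section 12.2.1 plans the proportion with a 95% confidence interval.

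**The concern.** Section 9.3 fixes the number of assessors, the qualification of one of them and that they evaluate independently, which most naturally means independently of each other. Nothing in the text keeps either assessor, or the third surgeon, apart from the operation. The surgeons who closed the wound and applied the device may therefore make every decision on the only primary endpoint.

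This matters most for a dehisced wound. Whether it counts in the primary endpoint depends on a judgement about infection. Dehiscence is not remote here: section 1.1 links perineal wound tension to it, and section 10.4 lists it among the expected adverse events. Two readers from one team can share the same leaning. If both call the wound uninfected, there is no disagreement and the third surgeon is never consulted.

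In a randomised comparison a lenient reading might affect both arms. Here the rate is set beside historical figures, so each SSI called uninfected lowers it with no offset. Section 1.3 also says the data will be the basis for a later large-scale trial, so a low rate would carry forward.

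**Working it through.** **Inputs.** From section 12.3: threshold 40%, expected rate 12%, enrolment 50. From section 12.2.1: a proportion with a 95% interval. Assumed, because the protocol gives no value: all 50 patients evaluable, a Clopper-Pearson interval, a share m of true SSIs missed (m = 0, 10%, 20%), and no false positives.

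**The plan's own figure.** Section 12.3 states 45 before dropouts. The two-group, continuity-corrected formula for 40% against 12% gives 45 per group, whereas one-sample calculations give about 19 to 20. That is a separate matter and does not affect this check.

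**Step 1: cut-off.** With 12 events in 50 the Clopper-Pearson upper limit is 38.2%; with 13 it is 40.3%. The interval lies wholly below 40% at 12 or fewer events.

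**Step 2: effect of missed SSIs.** Apparent rate = true rate × (1 − m). The chance of an interval below 40% is P(X ≤ 12), with X binomial on 50 patients at the apparent rate.

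| True rate | SSIs missed | Apparent rate | P(X ≤ 12) |
| --- | --- | --- | --- |
| 40% | 0% | 40.0% | 0.0133 (1.3%) |
| 40% | 10% | 36.0% | 0.0495 (4.9%) |
| 40% | 20% | 32.0% | 0.1436 (14.4%) |
| 12% | 0% | 12.0% | 99.5% |
| 12% | 10% | 10.8% | 99.8% |
| 12% | 20% | 9.6% | 99.9% |

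At a true rate of 40% an interval below 40% is a false conclusion, so those rows show the error that matters. At 12% the conclusion is correct and almost certain in every row. What changes is the estimate, which falls by 12.0 − 10.8 = 1.2 or 12.0 − 9.6 = 2.4 percentage points. Each relabelled wound moves the observed rate by 1/50 = 2 points.

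**Step 3: direction of the fix.** Let a and b be the two assessors' sensitivities and t the third surgeon's, with errors independent. Panel sensitivity is S = ab + [a(1 − b) + b(1 − a)]t. Its derivative in b is a(1 − t) + t(1 − a), which is never negative. Replacing one assessor by a more sensitive one therefore cannot lower S.

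Two examples, with 95% assumed for the outside assessor and a true rate of 40%:

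- Operators at 70%: S = 0.49 + 0.42 × 0.7 = 78.4%. With one outsider, S = 0.665 + 0.32 × 0.7 = 88.9%. P(X ≤ 12) falls from 16.6% to 5.6%.
- Operators at 80%: S = 0.64 + 0.32 × 0.8 = 89.6%. With one outsider, S = 0.76 + 0.23 × 0.8 = 94.4%. P(X ≤ 12) falls from 5.2% to 2.9%.

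These sensitivities are illustrative. The algebra shows the direction only if the outsider is indeed the more sensitive reader.

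**The case against.** The protocol does not leave the endpoint to one surgeon's impression. It has published definitions, a checklist, double reading and a tie-break, and nothing in it is contradictory. Who may serve as assessor could also be set in operational instructions or in the organisation pages, which are missing from the text reviewed. This stands as a reason to treat the point as a cheap improvement and not as an error.

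The objection also rightly limits several stronger readings that a reader might infer:

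- *The attending clinician's diagnosis is a second route to under-calling.* It is not. It is one of several alternative criteria, any one of which suffices, so it can only add SSIs. It cannot cancel pus or isolated organisms.
- *Under-calling sharply inflates the chance of success at intermediate rates.* At a true rate of 30%, P(X ≤ 12) does rise from 22% to 38% and 58% with 10% and 20% missed. But 30% is already below 40%, so an interval below 40% is correct there. Those figures do not measure false success.
- *The trial's conclusion is at risk under its own assumptions.* At 12% it is not.
- *The third surgeon must be a non-operator too.* That would require another board-certified surgeon who did not operate. The protocol gives no site staffing figures to show that every site has one.

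Finally, section 12.2.1 states no decision rule and names no interval method. A Wilson interval with 13 events has an upper limit of 39.6%, so the cut-off would move by one.

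**Conclusion.** The point holds as a bias-reducing design improvement. As written, section 9.3 permits both assessors of the sole primary endpoint to be operators, and the dehiscence rule gives their judgement a direct path to a lower rate.

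If the true rate were 40%, missing 10% or 20% of SSIs would raise the chance of a falsely favourable interval from 1.3% to 4.9% or 14.4%. At the planned 12%, only the estimate suffers, by 1.2 or 2.4 points. These sizes rest on assumed miss rates, 50 evaluable patients and a Clopper-Pearson interval. The documents do not show that under-calling will occur, nor that an outside assessor would be more sensitive; the latter is a reasonable expectation.

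The change reduces bias without removing it. Every patient receives the device, so an outside assessor is not blinded, and wounds never put forward for evaluation stay missed.

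**What to change.** Add one sentence to section 9.3: *At least one of the two assessors must not have taken part in the patient's operation.* State that a non-operating third surgeon is preferred where one is available, without making it a condition.

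Record in REDCap each assessor's decision and whether that assessor operated. This shows whether the rule was followed and allows operators' and non-operators' decisions to be compared.

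The cost is one sentence and two kinds of CRF entry per assessor. The panel stays at two assessors plus a tie-breaker. Only one of the two has to be a board-certified surgeon, so the non-operator may be another clinician. The downside is some scheduling burden at small sites.
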